### Safety outcomes

An adverse event is an incident that occurs after a patient or clinical trial subject receives a drug, but is not necessarily causally related to the treatment. All ICU staff will be instructed to pay attention to allergic reactions such as urticaria, shock and shortness of breath. These observations will be recorded on the participating patient’s data sheet and reported to investigators. Other extraordinary or questionable side effects will also be recorded.

Vital signs will be continually monitored and recorded in the ICU. The vital parameters include blood pressure, pulse, SpO_2_, temperature and respiratory rate. Blood counts, tests for infection, clinical chemistry biomarkers, and serum glucose will also be monitored. Prophylactic antibiotics will be used in all patients. If sepsis is suspected in the period when GC is given, treatment will follow the latest sepsis guidelines [13]. Electrolyte imbalance and hyperglycemia will also be corrected.

### Randomization and blinding

Block randomization will be conducted using a computer-generated random sequence, in blocks of size 4. Eligible patients will be assigned to one of the two study arms. A unique patient identification code will be generated to every screened patient without possible inference to patient identity.

Patients and researchers involved in data collection and analysis will be blinded. Doctors and nurses who will give the GC will not be blinded for allocations. These staff members will not be involved either in outcome evaluation or data analysis.

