## Materials and methods

### Setting

This study will be an investigator-initiated, prospective, single-blind, randomized, single-center study, which will investigate the effect of postoperative GC on patients with aTAAD. The trial will be conducted in the cardiac intensive care center of Zhongshan Hospital, Fudan University.

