### Overview

All patients with aTAAD undergoing surgery will be screened for study eligibility. Upon enrollment, eligible patients will be randomized 1:1 to one of the two treatment arms (i.e. GC or normal treatment) (Fig. 1). Data will be collected until hospital discharge or death.

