**Fig. 2 Fig2:**
[figure not shown]
Diagram of interventions

The first dose of MP will be given on the morning of postoperative day (POD) 1 at a dosage of 2 mg/kg/d, followed by another dose with the same dosage 12 h later. On POD 2 and POD 3, MP will be reduced to 1 mg/kg/d and 0.5 mg/kg/d respectively, with 12 h intervals between two injections.

All patients in the control group will receive treatments as usual without the administration of GC. Patients will be required to be supervised by medical personnel when administering the study drug, and their vital signs will be checked regularly in case of emergency.

Strategies to improve adherence to intervention and monitor adherence to procedures will be implemented. Three dedicated research fellows will screen all patients who enter the ICU after surgery. They will be responsible to check if certain candidate meets the study criteria. They will also be in charge of ensuring that intervention will be prescribed based on the protocol. In addition, two independent intensive care specialists will monitor adherence to interventions throughout the study period.

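### One published block size of 4, in a single-centre trial where the arm is visible to treating staff, makes up to a third of allocations predictable with certainty; undisclosed varying block sizes would remove nearly all of that at almost no cost

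*Protocol article*

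**What the plan says.** All of this comes from the protocol article.

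- **Randomization and blinding:** "Block randomization will be conducted using a computer-generated random sequence, in blocks of size 4". No variation in block size is stated. The same section says: "Doctors and nurses who will give the GC will not be blinded for allocations". Blinding is claimed for patients and for researchers who collect or analyse data; the screening fellows are not named.
- **Overview and Setting:** "eligible patients will be randomized 1:1 to one of the two treatment arms", in an "investigator-initiated, prospective, single-blind, randomized, single-center study". No stratification is stated, so the article describes one running sequence.
- **Intervention, control arm:** "All patients in the control group will receive treatments as usual without the administration of GC". No placebo is mentioned, so the arm can be seen at the bedside.
- **Intervention, fellows:** "Three dedicated research fellows will screen all patients who enter the ICU after surgery". On eligibility: "They will be responsible to check if certain candidate meets the study criteria". On treatment: "They will also be in charge of ensuring that intervention will be prescribed based on the protocol".
- **Inclusion criteria and Clinical definitions:** a patient must be expected to survive more than three days after surgery. The infection that leads to exclusion can be diagnosed from clinical signs without a pathogen test. Both leave room for judgement.

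**The concern.** In a block of 4 with two places per arm, anyone who has followed the arms so far knows the next one as soon as one arm has used both its places. Hiding the list, by envelopes or a central service, does not prevent this, because the deduction needs only the block size and the past arms.

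The block size is printed in the article. The past arms are visible to treating staff, and the fellows need to know a patient's arm to see that the right treatment is prescribed. The same fellows decide whether the next candidate is eligible. Someone who knows which arm comes next could, deliberately or not, read a borderline criterion differently according to the patient's outlook. The arms would then differ at entry, and the comparison of SOFA change would carry that difference.

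**Working it through.** **1. The plan's own figures, used as the base.** From Sample size: control decline 2.87, SD 1.69, a 25% larger reduction with glucocorticoids, two-sided α = 0.1, power 0.9.
- Planned effect: 0.25 × 2.87 = 0.7175 points.
- Per arm: 2 × (1.645 + 1.282)² × 1.69² / 0.7175² ≈ 95.03, rounded up to 96, as stated; 192 in total.
- With dropout: 192 × 1.1 = 211.2, rounded up to 212, as stated.

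**2. Predictability with fixed blocks of 4.** There are 6 equally likely arrangements of 2 + 2. The observer knows the block size and the past arms in order, guesses the arm with more places left, and tosses a coin when tied.

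| Place in block | Certain | Best guess correct |
|---|---|---|
| 1st | 0 | 1/2 |
| 2nd | 0 | 2/3 |
| 3rd | 1/3 | 2/3 |
| 4th | 1 | 1 |

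- Certain: (0 + 0 + 1/3 + 1)/4 = 33.3%, that is 64 of 192 or about 71 of 212.
- Guessed correctly: (1/2 + 2/3 + 2/3 + 1)/4 = 70.8%, against 50% by chance.

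**3. Predictability after a change.** A larger fixed block helps only partly: exact enumeration gives 25% certain for blocks of 6 and 20% for blocks of 8. For a random mix of 4, 6 and 8, I used 400 simulated trials of 212 patients. The observer knew which sizes were in the mix but not their order, and updated by Bayes' rule. The result was 2.1% certain (0.021 × 212 ≈ 4 patients) and 68.0% guessed correctly. Staff who do not know the sizes in the mix would have less to go on.

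**4. What this could mean in SOFA points.** The documents do not say how far steering could move SOFA change, so the shift *s* is an assumption, shown over a range. Suppose staff act only when certain, so that the expected change moves by +*s* when one arm is known to be next and by −*s* when the other is. Then bias = 2 × *s* × (share certain).

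| Assumed *s* | Blocks of 4 (2*s*/3) | Share of 0.7175 | Undisclosed 4/6/8 (2*s* × 0.021) |
|---|---|---|---|
| 0.10 | 0.07 | 9% | 0.004 |
| 0.25 | 0.17 | 23% | 0.01 |
| 0.50 | 0.33 | 46% | 0.02 |

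**5. If staff acted on every best guess instead.** Bias = 2 × *s* × (2 × guess rate − 1). For blocks of 4 this is 2 × *s* × (2 × 0.7083 − 1) = 0.833*s*. For undisclosed 4/6/8 it is 2 × *s* × (2 × 0.680 − 1) = 0.72*s*. So 0.72/0.833 = 86% of the bias would remain. Varying the sizes helps against certainty, and little against informed guessing.

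**The case against.** **The fellows' knowledge is inferred.** The article does not say that each fellow sees every arm, follows the enrolment order or makes use of the block size. This stands. The one-third figure is conditional on that knowledge. The inference is still a strong one, since the fellows' duties put eligibility and prescription in the same hands in one unit.

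**A condensed article may leave the assignment mechanism to the full protocol.** This also stands, and nothing here rests on its absence. A reader might infer that concealment is missing, or that allocations are released before eligibility is settled; the article supports neither. The point concerns the block size that is stated, which a concealed list does not protect.

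**Data researchers are blinded.** That protects assessment. Selection happens before allocation, and the fellows are not named among the blinded.

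**The room for steering is limited.** Many criteria are factual, such as pregnancy, an implanted device or a Child-Turcotte-Pugh score of 10 to 15. Every patient is screened and every screened patient receives a code, so selective exclusion could leave a trace. These features narrow the exposure but do not prevent prediction.

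**Such bias might be thought beyond repair in analysis.** That is too strong. SOFA on postoperative day 1 is measured before the study drug, and EuroSCORE II, bypass duration and CRP are planned subgroup factors. Selection on recorded factors could be examined and partly adjusted for. Selection on unrecorded prognosis could not.

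**The direction is unclear.** The outcome is change from baseline, so choosing patients with a better outlook need not mean choosing those whose SOFA falls more. This is why the SOFA figures are shown only as a range of assumed shifts.

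**Conclusion.** The point holds as a cheap design improvement. For an observer who knows the block size and the past arms in order, 33.3% of allocations (about 71 of 212) are certain and 70.8% can be guessed; this arithmetic is exact. That the fellows are such observers is very likely from their duties but not stated.

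A reader might go further and conclude that the trial will be biased, or that varying the block sizes would cure the whole exposure. The documents show exposure only, and the change leaves informed guessing at about 68%. The SOFA figures of 0.07 to 0.33 points rest entirely on the assumed shifts of 0.10 to 0.50 and on steering only when certain.

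**What to change.** Generate the list, or its remainder if recruitment has begun, with randomly varying block sizes, for example 4, 6 and 8. Do not disclose the sizes to site staff, and do not publish them while patients are being enrolled. In Randomization and blinding, replace the fixed size with a statement that block sizes vary at random and are withheld from site staff.

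The cost is one regenerated list and one sentence. With blocks of 4, 212 patients make 53 complete blocks and equal arms. With a largest block of 8, the arms could differ at the end by at most 8/2 = 4 patients (for example 108 and 104), which is negligible for precision.

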### ***Data to be collected*** (Table 1)

**Table 1 Tab1:** Data to be collected

Time Points	Day of ICU admission	Treatment					
		Preoperative	Pre-drug	24 h	48 h	72 h	Discharge or death
Enrollment	x						
Informed consent	x						
Inclusion and exclusion criteria	x						
Demographics^a^	x						
Past medical history^b^	x						
Pre-operative cardiac function^c^	x						
Operative information^d^	x						
Assessment							
Temperature		x	x	x	x	x	
Respiratory rate		x	x	x	x	x	
Heart rate		x	x	x	x	x	
Systolic blood pressure		x	x	x	x	x	
Diastolic blood pressure		x	x	x	x	x	
SOFA score	x			x	x	x	
Methylprednisolone administration				x	x	x	
Inflammatory indicators^e^		x	x	x	x	x	
Blood count^f^		x	x	x	x	x	
Blood biochemistry^g^		x	x	x	x	x	
Arterial blood gas^h^		x	x	x	x	x	
Concomitant medications^i^		x	x	x	x	x	
Adverse events^j^				x	x	x	x
24 h fluid intake and output		x	x	x	x	x	

*TIA* Transient ischemic attack, *COPD* Chronic obstructive pulmonary disease, *DM* Diabetes mellitus, *NYHA* New York Heart Association, *LVEF* Left ventricular ejection fractions, *TAPSE* Tricuspid annular plane systolic excusion, *ECG* Electrocardiogram, *ALICE* Albumin-indocyanine green evaluation, *ICU* Intensive care unit, *CCB* Calcium channel blockers, *CRP* C-reactive protein, *PCT* Procalcitonin, *ESR* Erythrocyte sedimentation rate, *TNFα* Tumor necrosis factor-α, *IL-6* Interleukin-6, *IL-10* Interleukin-10, *pH* potential of Hydrogen, *CRRT* Continuous renal replacement therapy

^a^age, sex, height(cm), weight(kg), smoking and alcohol consumption

^b^pre-existing definite preoperative diagnosis; previous or screening period medical history (including at least hypertension, TIA, COPD, stroke, DM, various arrhythmias, peptic ulcer)

^c^preoperative NYHA classification, preoperative cardiac ultrasound including LVEF, TAPSE, preoperative ECG, myocardial enzyme profile, preoperative ALICE score for entrapment

^d^name of the procedure, duration of the procedure (min), time outside the body (min), time of block (min), time of transfer to the ICU. Intraoperative dose and time of hormone use, blood loss, and transfusion volume; β-blockers, CCB, anticoagulants such as aspirin, antiplatelet agents, antihypertensive agents, cardiotonic agents, proton pump inhibitors or H2-blockers, antibiotics used within the previous 7 days

^e^CRP, PCT, ESR, TNFα, IL-6, IL-10

^f^hemoglobin, white blood cell, neutrophil count, lymphocyte count, platelet count

^g^alanine aminotransferase, aspartate aminotransferase, total bilirubin, direct bilirubin, serum creatinine, plasma brain natriuretic peptide precursor, serum troponin T

^h^pH, partial pressure of oxygen, partial pressure of carbon dioxide, electrolytes (potassium ion, sodium ion), blood glucose

^i^β-blockers, CCB, anticoagulants such as aspirin, antiplatelet agents, antihypertensive drugs, cardiotonic drugs

^j^occurrence of various infections, CRRT, cerebrovascular events, gastrointestinal bleeding or perforation, cardiogenic shock, etc

Assessment of organ dysfunction: SOFA score.

Investigational medication: methylprednisolone.

Patient's inflammatory indicators (high sensitivity C-reactive protein, Procalcitonin, Tumor Necrosis Factor α, IL-6, IL-10).

Blood count: hemoglobin, white blood cell, neutrophil count, lymphocyte count, platelet count.

Blood biochemistry: alanine aminotransferase, aspartate aminotransferase, total bilirubin, direct bilirubin, serum creatinine, plasma brain natriuretic peptide precursor, serum troponin T.

Blood gas analysis: PH, partial pressure of oxygen, partial pressure of carbon dioxide, electrolytes (potassium ion, sodium ion), blood glucose.

Concomitant medications: β-blockers, calcium channel blockers, anticoagulants, antiplatelet agents, antihypertensive agents, cardiotonic agents, proton pump inhibitors or H2-blockers, antibiotics used within the previous 7 days.

Adverse events: occurrence of infections, gastrointestinal bleeding or perforation, etc.

Vital signs: including blood pressure, pulse rate, respiratory rate, body temperature.

### Data collection and storage

Blinded trial investigators will enter the baseline characteristics, process variables, and outcome data from the patient files into web-based case report forms (Electronic Data Capture System) from POD 1 to POD 4, and follow up at discharge from hospital. Calculation of the SOFA score will be done by the on-duty physician. Personal information about potential and enrolled participants will be collected and maintained. The initial of patient’s full name will be used instead of the real name to identify certain patients. In addition, during the study period, a unique identification number will be used as the dominant way to follow certain patients to protect confidentiality. If necessary, information stored in the electronic patient record will be used for follow-up and patients or their surrogates will be contacted directly if additional data is needed. Data will be stored in a third-party system and the trial investigators have full access to it.

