### Outcomes

The primary outcome will be the difference of Sequential Organ Failure Assessment (SOFA) score on POD 4 compared to baseline (on POD1 before MP administration).

Secondary outcomes will be in-hospital mortality, days of ICU stay; days of hospital stay; duration of mechanical ventilation; tracheotomy; continuous renal replacement therapy; postoperative infection; inflammatory markers on POD 1, 2 and 3; composite endpoint (in-hospital morbidity and mortality or ICU stay over 30 days or tracheotomy).

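### The primary outcome, SOFA, is calculated by the on-duty physician with no blinding condition, so the blinded outcome evaluation promised elsewhere in the protocol is not secured

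*Protocol article*

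**What the plan says.** The Outcomes section defines the endpoint: "The primary outcome will be the difference of Sequential Organ Failure Assessment (SOFA) score on POD 4 compared to baseline", with baseline taken on POD 1 before the first methylprednisolone dose.

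Randomization and blinding makes three statements:

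- On those kept unaware of allocation: "Patients and researchers involved in data collection and analysis will be blinded".
- On the treating side, by contrast: "Doctors and nurses who will give the GC will not be blinded for allocations".
- Of those doctors and nurses: "These staff members will not be involved either in outcome evaluation or data analysis".

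Data collection and storage then describes two roles. For data entry: "Blinded trial investigators will enter the baseline characteristics, process variables, and outcome data from the patient files into web-based case report forms". For the score itself: "Calculation of the SOFA score will be done by the on-duty physician".

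On the comparator, the Intervention section states: "All patients in the control group will receive treatments as usual without the administration of GC". It describes no placebo or sham injection. The active arm receives injections every 12 hours over POD 1 to POD 3.

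**The concern.** The blinding section gives an explicit safeguard: people who know the allocation do not evaluate outcomes. The data section gives the calculation of the only primary outcome to a clinician on the ICU rota. It names that clinician separately from the blinded investigators and does not say that he or she is blinded. With twice-daily injections in one arm and nothing corresponding in the other, a physician on duty would ordinarily know who is treated.

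Blinded data entry does not repair this. If the score has already been assigned by someone aware of the allocation, the blinded investigator only copies it.

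SOFA mixes laboratory values, which leave little room for judgement, with inputs assessed at the bedside, such as consciousness. The planned treatment effect is below one SOFA point, so a modest systematic difference in scoring between arms would matter. If raw components are not captured during the trial, the score may not be recoverable by a blinded person afterwards.

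**Working it through.** **Setting the sections side by side**

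1. Not blinded: the clinicians who administer the steroid (Randomization and blinding).
2. Excluded from outcome evaluation: those same clinicians (same section).
3. Calculates the primary outcome: the on-duty physician (Data collection and storage). No statement places this physician outside the group in item 1, and none says that he or she is blinded.
4. Blinded: patients and the researchers who collect and analyse data. In the data section the blinded investigators transcribe from patient files; the calculation is assigned to someone else.
5. Concealment at the bedside: none described, since controls have usual care without a placebo.

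Items 2 and 3 are compatible only if the on-duty physician is separate from the treating staff and shielded from the drug chart. The protocol says neither.

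**How sensitive the primary comparison is**

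Inputs from the Sample size section: decline in SOFA 2.87 with SD 1.69; 25% larger decline assumed under glucocorticoid; two-sided α = 0.10; power 0.90; 96 per group.

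Reproducing the plan's figure first:

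- Target difference: 0.25 × 2.87 = 0.7175 points.
- n per arm = 2 × (1.645 + 1.282)² × 1.69² / 0.7175² ≈ 95.0, just above 95, which rounds up to 96. This matches the plan.

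Standard error of the difference at that size: 1.69 × √(2/96) = 0.2439 points.

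The documents give no figure for scoring bias, so its size *b* is an assumption. With no true effect and a net shift *b* in favour of one arm, the two-sided rejection probability is Φ(b/SE − z) + Φ(−b/SE − z). Here z = 1.96 for the 5% level given under Data analysis, and z = 1.645 for the 10% level used in the sample size.

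| Assumed net shift at POD 4 | Share of 0.7175 | b/SE | Error rate at 5% level | Error rate at 10% level |
|---|---|---|---|---|
| 0.10 | 14% | 0.41 | 6.9% | 12.8% |
| 0.25 | 35% | 1.02 | 17.6% | 27.1% |

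A shift of 0.10 arises if one component is scored one point lower in 10% of glucocorticoid patients and in no controls. A shift of 0.25 arises if that happens in 25% of them.

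The outcome is a change score. The same leniency applied at baseline and at POD 4 would cancel, so the table concerns only scoring that differs between arms at POD 4 beyond any difference at baseline.

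**The case against.** The strongest reply is that the conflict is inferred. The protocol does not say that the on-duty physician gives the drug or knows the allocation. A charitable reader could count that physician among the blinded researchers who collect data. The trial is also labelled single-blind, which by itself promises nothing about assessors. This stands in part: a reader might conclude that the protocol assigns the primary outcome to a person it declares unblinded, and it does not go that far. What remains is that the safeguard in the blinding section is not carried through. The scorer is named apart from the blinded investigators, and no means is given by which a physician on an ICU with open treatment would stay blinded.

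Two further inferences are tempting and are not supported:

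- *That the blinded investigators are unblinded by their own form.* Table 1 has a row for "Methylprednisolone administration", but the protocol does not say who completes it. The Intervention section gives oversight of prescribing and adherence to research fellows and independent specialists, who could supply it.
- *That the score cannot be rebuilt from the case report form.* Table 1 and the lists after it do not name a consciousness score, inspired oxygen fraction or vasopressor dose. They are a journal condensation, however, and SOFA has its own row whose underlying fields are not shown.

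The size of any bias is also unknown. Laboratory-based components are little exposed, and at a shift of 0.10 points the error rate moves only from 5% to about 7%.

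Finally, deriving the score by program does not blind a consciousness assessment made at the bedside, and investigators reading patient files may come across the drug order. Both points are right. They limit what the remedy achieves, but they do not remove the need for it.

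**Conclusion.** The concern holds in a limited form. The protocol promises that unblinded treating staff stay out of outcome evaluation, then gives the primary outcome to the on-duty physician without saying that this person is blinded or separate. Blinded evaluation of SOFA is therefore claimed but not secured. That the physician knows the allocation is likely, given open treatment without placebo, but it is an inference.

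The resulting detection bias has unknown size and direction. The error rates of about 7% and 18% at the 5% level rest on assumed shifts of 0.10 and 0.25 points, an SD of 1.69 in both arms, 96 analysed patients per arm and a normal approximation. They show how little differential scoring would matter against a target of 0.72 points; they do not estimate what will happen. Because the gap concerns the sole primary outcome and may not be repairable once data are collected, it should be corrected in the protocol.

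**What to change.** Reconcile Randomization and blinding with Data collection and storage:

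1. Replace the on-duty physician's calculation with a programmed derivation of SOFA in the EDC system, from raw component values entered by the existing blinded investigators.
2. Confirm that the full case report form holds every component: arterial oxygen and inspired oxygen fraction, platelets, bilirubin, mean arterial pressure and vasopressor dose, consciousness score, creatinine and urine output. Add any that are absent.
3. Have unblinded staff record methylprednisolone administration on a separate form that the blinded investigators do not complete.
4. State plainly that inputs judged at the bedside, such as the consciousness score, remain unblinded, and add a sensitivity analysis of SOFA change without that component.

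The cost is a short protocol correction, a change to the case report form and EDC system with possibly a few more fields per visit, and one more analysis. No additional assessor and no change to sample size or treatment is needed. Residual unblinding remains for the bedside score, and possibly for investigators who read patient files; the protocol should acknowledge both.
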